## Abstract

**Introduction:**

Although the effects of ionizing radiation on radiation workers have been extensively studied in China, no prospective cohort study has been conducted in Chongqing. Furthermore, previous cohorts have not provided a broad-gauge assessment of the temporal relationship between low-dose occupational radiation exposure and the risk of health outcomes.

**Methods:**

A prospective cohort study will be carried out focusing on radiation workers in Chongqing. Health examination outcomes and radiation dose monitoring data will be collected and analyzed using the distributed lag non-linear model (DLNM) combined with generalized additive model (GAM) or generalized linear model (GLM) to evaluate the exposure-lag response relationship.

**Discussion:**

Our study will enhance our understanding of the exposure-lag response association between occupational radiation exposure and the health of radiation workers based on DLNM.

**Clinical trial registration:**

Chinese Clinical Trials Registry, ChiCTR2400081804.

## Introduction

1

Ionizing radiation is extensively applied in medicine, industry, and other fields. Ionizing radiation can induce cell death, impair the integrity of organs and tissues, and impair their function, which are collectively known as the biological effects, including deterministic and stochastic effects (1). The severity of deterministic effects increases as absorbed doses rise, and a threshold dose was required to observe injuries (1). Early effects include skin burns, reduced blood cell levels, and other symptoms. Later-occurring effects include cataracts, necrosis, hypothyroidism, and cardiovascular disorders (1). Absorption of ionizing radiation energy by genetic material in cells causes DNA damage, leading to cell death, chromosomal aberrations, and gene mutations (2), developing genetic diseases in the offspring of an irradiated individual or cancer, defined as stochastic effects (3). In addition, ionizing radiation exposure can damage liver and kidney function, and a few studies have proved this (4, 5).

With the continuous development of radiodiagnosis and therapy technology, the number of radiation workers in the medical field has significantly increased, around 600,000 radiation workers in China, with around 400,000 of these individuals engaged in medical occupations (6). Despite the use of appropriate personal protective equipment by radiation workers, they remain inevitably subject to chronic low-dose occupational radiation (7). Long-term exposure to low-dose ionizing radiation alter immune fitness, and increased risks of cardiovascular diseases and solid cancer (8–10). Among these health outcomes, cancer remains the primary focus of most epidemiological and cohort studies examining occupational radiation exposure (11, 12). The effects of ionizing radiation on radiation workers have been extensively studied in at least eight countries (Canada, the United Kingdom, Russia, Korea, Finland, France, Germany, Sydney, and the United States) (9, 13–30). Some cohort studies conducted nationally and through international collaborations, were characterized by their large scale and extended follow-up periods, for example, in a collaborative cohort of 15 countries, the study population comprises up to 407,391 individuals (21), in another study investigating the risk of malignant skin tumors among radiation workers, the follow-up period extended to about 70 years (30). However, the exposure-lag response associations between chronic low-dose ionizing radiation exposure and various adverse health outcomes have been not well-studied, with the exception of cancer (9, 31).

The exposure-lag response was delineated by Gasparrini regarding the temporal relationships between exposure and the risk of a health outcome (32). Quantitative exposure studies often use cumulative metrics, but lack detailed time-varying intensity data for the low-dose ionizing radiation exposure, while duration metrics omit intensity information (33). The exposure-lag response could explain the relative importance of intensity, duration, and timing of the low-dose ionizing radiation exposure in relation to various adverse health outcomes (10, 31–33). To address the exposure-lag response, we proposed to establish a prospective cohort in Chongqing characterized by personal radiation exposure dose, long follow-up duration, and relative various adverse health outcomes.

## Methods and analysis

2

### Study population and design

2.1

The THECORW study is a prospective cohort study. A total of 825 radiation workers will be recruited in Chongqing from 2024 to 2044. The study aims to include radiation workers in Chongqing. In accordance with the regulations on occupational health management of radiation workers issued by the National Health Commission of China, occupational health management is mandated for all radiation workers nationwide (34). Consequently, all radiation work units in Chongqing are required to organize regular occupational health examinations for radiation workers, with the interval between two consecutive examinations not exceeding 2 years (34). Radiation workers registered in the Chongqing CDC personal dose monitoring system will receive information about the study during their annual occupational health examinations from our investigators. Workers who consent to participate will provide written informed consent before enrollment. Those meeting the inclusion criteria will be enrolled in the study. Following enrollment, their personal dose monitoring data from the Chongqing CDC personal dose monitoring system will be integrated with health data from National Radiation Health Information Platform via personal identification numbers (35). Participants will retain the right to withdraw from the study at any time and for any reason without any consequences.

### Inclusion and exclusion criteria

2.2

Included in the study will be radiation workers who are: (1) consistently wear dose dosimeters; (2) regular occupational health examination at the Chongqing Center for Disease Control and Prevention (CDC); (3) over 18 years old; (4) no communication barriers (34, 36). Excluded from the study will be those who are with a history of chromosomal aberrations, micronucleus abnormalities, peripheral blood abnormalities and blood-related diseases, abnormal liver and kidney function, cancer, history of abnormal thyroid hormones and thyroid-related diseases, and cataract and glaucoma (34, 36).

### Sample size calculation

2.3

Radiation exposure damages hematopoietic tissues, which is characteristic of occupational exposure. It has been proven that the hematological system, including mature functional cells, is susceptible to ionizing radiation (36). Ionizing radiation can cause early damage to the hematological system, therefore, blood cell counts are commonly used to assess its effects, a method widely used in the field (36).

The complete blood count served as the basis for sample size calculation. A sample size of 825 is considered sufficient to allow studies of the impact of radiation on human health. For example, according to references, the white blood cell count is commonly used to assess the effects of radiation on the health of a population (3, 4). The average white blood cell count for the population in the Chinese radiation group is (6.34 ± 1.40)*10 (9)/L, and in the normal population group is (6.59 ± 1.39)*10^9^/L.^5^ For a type I error of 0.05, a type II error of 0.1, and a power of 0.9, the sample size required is 660. Considering a 20% loss in follow-up (37, 38), the sample size increases to 825. Therefore, a recruitment sample of 825 radiation-exposed individuals will have sufficient power for the study. The sample size was estimated using G*Power software version 3.1 (Heinrich-Heine-Universität Düsseldorf, Düsseldorf, Germany) (39).

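### The 660 (825 with loss) is the size of one group in an exposed-versus-unexposed comparison that the study does not contain, so the stated 90% power applies to no planned analysis

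*Protocol article*

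**What the plan says.** Section 2.3 (Sample size calculation) takes the complete blood count as its basis and works through white cell count. The inputs, in units of 10^9/L, are two group summaries: "The average white blood cell count for the population in the Chinese radiation group is (6.34 ± 1.40") and "in the normal population group is (6.59 ± 1.39"). The error rates and the result follow in one sentence: "For a type I error of 0.05, a type II error of 0.1, and a power of 0.9, the sample size required is 660". Loss is then added: "Considering a 20% loss in follow-up (37, 38), the sample size increases to 825". The section concludes that "a recruitment sample of 825 radiation-exposed individuals will have sufficient power for the study".

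Section 2.1 sets enrolment at the same number: "A total of 825 radiation workers will be recruited in Chongqing from 2024 to 2044". Section 2.2 admits radiation workers who wear dosimeters and describes no unexposed group. Section 2.5 plans a distributed lag non-linear model (DLNM) with a cross-basis of dose and lag, fitted with a GLM or GAM. The only controls it mentions are time-matched controls in an optional nested case-control design.

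Section 2.3 does not name the test, its sidedness or the allocation ratio.

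**The concern.** The calculation uses two groups, but the conclusion concerns one. A difference between exposed and unexposed means can be tested at the planned power only if the unexposed people are also measured, and the article describes no such people. The planned analysis also asks a different question: how white cell count varies with the amount and timing of dose among workers who are all exposed. Power for that depends on the size of the dose effect, the spread of dose, the degrees of freedom of the cross-basis and the correlation between repeated blood counts in the same worker. None of these enters the calculation.

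This is the only power statement for a study dated 2024 to 2044, and the complete blood count is its primary outcome. If it stands, a flat dose-lag result could be reported as a negative finding with 90% power, which nothing in section 2.3 supports.

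**Working it through.** **Inputs from section 2.3.** Means 6.34 and 6.59, difference 0.25. SDs 1.40 and 1.39, pooled SD = √((1.40² + 1.39²)/2) = 1.395. Standardised difference d = 0.25/1.395 = 0.179. Alpha 0.05, power 0.90, loss 20%. Two-sided testing and 1:1 allocation are inferred, because that combination returns the printed figure.

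**Reproducing 660.** For two independent means,

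n per group = 2 × (1.960 + 1.282)² × (SD/difference)², where (1.960 + 1.282)² = 10.507 before rounding the quantiles.

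- SD 1.395: 2 × 10.507 × (1.395/0.25)² = 654.3, so 655 per group. The exact noncentral-t calculation gives 656.
- SD 1.40: 2 × 10.507 × (1.40/0.25)² = 659.0, so 660 per group. The exact calculation also gives 660, with power 0.90001.

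The printed figure is therefore a per-group number. The two-group total is 2 × 656 = 1,312 to 2 × 660 = 1,320.

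**Loss.** 660/(1 − 0.20) = 825. The division is right, but 825 is then one group as well. Two groups would be 1,320/0.80 = 1,650 recruited, half of them unexposed.

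**Other readings of 660.**

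| Reading | Result |
|---|---|
| Two-sided, 1:1, size of one group | 656 to 660: matches |
| Two-sided, 1:1, total of two groups | 1,312 to 1,320 |
| One-sided, 1:1 | 534 per group, 1,068 in total |
| One sample against a fixed 6.59, two-sided | 10.507 × (1.40/0.25)² = 329.5, so 330 (332 by exact t) |
| 80% power, two-sided, 1:1 | 489 per group, 978 in total |
| Allocation 2:1 to 4:1 at 90% power | no group size or total near 660 |

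**What 660 would deliver under the two tempting readings.** Split as 330 + 330, two-sided power for the 0.25 difference is 63%. Against a fixed mean of 6.59, power is 99.6%. Neither is 90%.

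**Calculation against design.** Section 2.3 needs two groups of 660. Sections 2.1 and 2.2 supply one, all exposed. Section 2.5 compares neither group with a normal population; it regresses outcomes on dose and lag within the cohort.

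**The case against.** The arithmetic in section 2.3 is not wrong: 660 follows from its inputs and 825 follows from 660. That stands. The fault is a mismatch between the calculation and the study, not a slip in computation.

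The test, sidedness and allocation are inferred. That also stands, though none of the other standard variants tried comes near 660.

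A full protocol that is not shown might describe an external comparison sample. That would soften the point about the missing group. It would not give the dose-lag model a power, because the calculation contains nothing about dose.

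The article introduces the white cell calculation as an example, and its Discussion recommends larger samples in future. Neither removes the unqualified conclusion in section 2.3, and the Discussion also describes the planned sample as large enough.

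A reader might infer that the cohort is underpowered. The document does not support that. It gives no dose effect, dose spread, spline degrees of freedom or within-person correlation, so power for the planned model cannot be computed. Trial calculations show how open the question is. Assume one observation per worker, 660 workers, and a linear effect of 0.25 at mean dose. With a dose coefficient of variation of 0.25, 0.5 or 1.0, power is 21%, 63% or 99.6% for a single linear term and about 10%, 30% or 93% for a 9-df cross-basis. All of these inputs are assumptions. Workers are also examined at least every 2 years, so there will be repeated counts. With 10 visits, a time-fixed dose, a within-person correlation of 0.5 and a coefficient of variation of 0.5, the 63% becomes about 87% and the 30% about 54%.

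A reader might also point to Table 1, where the 2016 white cell count is 5.72 ± 1.46, as evidence that the planning SD is wrong. The table covers 50 workers. A 95% interval for that SD is about 1.22 to 1.82, which contains 1.40, and the absolute mean does not enter the formula.

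**Conclusion.** The concern holds as a mismatch between the power calculation and the design and analysis. The 660, and hence the 825, is the size of one group in a comparison that needs about 1,312 to 1,320 evaluable people, half of them unexposed and not in the design. The stated 90% power, and the conclusion that 825 exposed workers suffice, do not apply to any analysis the article plans. This rests on the inferred 1:1, two-sided t-test and on the article describing no comparison sample; the mismatch with the dose-lag model does not depend on either. Whether 825 workers are too few, enough or more than enough for that model is unknown from this document.

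**What to change.** Keep 825 and rewrite section 2.3:

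1. Withdraw the statement of 90% power and the conclusion drawn from it.
2. State that 660 is the per-group number of an exposed-versus-unexposed comparison of means that is not part of the study, and name the test, sidedness and allocation behind it.
3. Report the effect that the planned DLNM can detect with 660 evaluable workers. Obtain it by a short simulation using the dose distribution already held in the Chongqing CDC monitoring system, each worker's repeated examinations with a stated range of within-person correlation, and the planned cross-basis degrees of freedom.
4. If a closed-form figure is wanted, give it only as a labelled one-observation-per-worker simplification. At n = 660 and 90% power, the detectable R² is about 1.6% for a 1-df dose term and about 3.0% for a 9-df cross-basis.

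The cost is a reworded section and a small calculation, with no added participants. The stated power becomes conditional on assumptions; whether it is higher or lower than 90% depends on what the simulation shows.

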### Dosimetry data

2.4

Radiation dose data were collected based on the Chongqing CDC’s personal dose monitoring system, which integrates various functions, including sample collection and distribution, dose allocation and input, report generation, annual dose statistics and inquiries, and charge management (40). In addition, it provides functions supporting the entire monitoring process, such as new system management, automatic generation of periodic test reports, and annual dose reports (40).

The annual radiation exposure dose for workers is less than the threshold (20 mSv), consequently, the individual dose equivalent Hp (10) was used to evaluate the effective occupational exposure dose (6, 41). The annual effective dosage is defined as the cumulative dose equivalent over four successive monitoring periods (3 months each) (41).

The effective dose (E) was calculated using the following equation: where W_T_ represents the weighting factor of each tissue, W_T_ is the tissue weight factor of the exposed organ or tissue, and H_T_ is the equivalent dose of the main exposed organ or tissue (42).
$$E=\underset{T}{\sum }W_{T}\cdot H_{T}$$

Nuclear medicine and interventional radiology workers were required to wear two personal dosimeters, both inside and outside lead clothing, to estimate the radiation dose (42). The following equation was used to calculate the effective dose of external radiation: *α* and *β* are the coefficients (The coefficients are different with or without thyroid shielding), H_m_ is the Hp (10) measured by a personal dosimeter worn inside the lead apron (43), H_n_ is the Hp (10) measured by a personal dosimeter worn on the outer collar of a lead apron (42).
$$E=\alpha \;H_{m}+\beta \;H_{n}$$

The collective effective dose denotes the sum of the effective doses for all radiation workers, S represents the collective effective dose, X_i_ is the effective dose, n is the total number of workers (44–46), the equation as follows:
$$S=\overset{n}{\underset{i=1}{\sum }}\;X_{i}$$

The organ dose estimation refers to the International Commission on Radiological Protection (ICRP) 116 organ dose conversion factor and irradiation geometry factor (47, 48). The equation is as follows: D_T_ is tissue or organ dose (Gray); H_p_(d) is badge dose measurement when calibrated as personal dose equivalent (Sv or rem); K_a_ is air kerma (Gray) (49).
$$D_{T}=H_{p}\left(d\right)\left[\;\left(\frac{D_{T}}{K_{a}}/\frac{H_{p}\left(d\right)}{K_{a}}\right)\;\right]$$

Estimation of eye lens dose: D_L_ present absorbed dose to the eye lens (mGy); f _(q):_ conversion coefficient from personal dose equivalent to absorbed dose of eye lens; H_p_(d): personal dose equivalent (mSv). H_P_ (3) is the personal dose equivalent at a depth of 3 mm in soft tissue and is used for measuring lens dose (50, 51).
$$D_{L}=f_{q}\;Hp_{\left(d\right)}$$

### Statistical analysis

2.5

Health examination outcomes and individual dose monitoring data will be collected from Chongqing CDC personal dose monitoring system and National Radiation Health Information Platform (35, 40). Data quality will be assessed using the “dataquieR” package in R software, following the framework proposed by Schmidt et al. (52, 53). If radiation dose data is missing, we can use the notional dose to supplement the missing data, which represented the average dose for the same occupation during that year (54). The exposure–lag–response association between radiation dose and health outcomes will be evaluated using a distributed lag non-linear model (DLNM) combined with either a generalized linear model (GLM) or multiple generalized additive models (GAM) (55). For certain outcomes, if necessary, a nested case–control design will be applied, with controls time-matched to cases to ensure a comparable number of total person-time observations. A cross-basis function in the DLNM, utilizing natural spline basis functions, will be employed to construct a two-dimensional matrix that integrates radiation dose and lag time, thereby enabling a detailed analysis of the lag structure (55). For continuous health outcomes, a Gaussian distribution will be used as the link function; for count outcomes, a Poisson distribution will be applied; and for categorical outcomes, a binomial distribution will be employed in the GLM framework. Given the non-linear relationship between radiation dose and health outcomes, GAM will be applied to assess potential dose–response relationships. For non-linear relationships, piecewise linear spline models will classify participants into different exposure categories based on radiation exposure thresholds and will use these categories to assess linear dose–response relationships. Several sensitivity analyses were conducted to assess the robustness of the results. First, GAM or GLM analyses will be rerun after excluding cases with missing data for both controls and cases. Second, to account for potential interaction effects, interaction models were fitted by including variables such as exposure dose levels, age, gender, and occupational category in relation to health outcomes. Third, if significant interaction effects were identified, stratified analyses were performed, such as by occupational category or exposure dose levels, to explore these effects further. All analyses were carried out using R software (version 4.4.1). For normally distributed data, continuous variables are presented as mean ± standard deviation (SD); skewed data are presented as median or interquartile range (IQR). *p* values <0.05 were considered as statistically significant.

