Several cohort studies on occupational radiation exposure have been conducted in China, primarily examining outcomes such as cancer incidence and mortality (13, 72), changes in thyroid hormones (41) and complete blood count (73), liver damage (74), cataracts (66). A three-year cohort study showed that long-term low-dose radiation exposure was a risk factor for liver injury (74). In addition, a prospective cohort study explored the effects of occupational radiation exposure on platelets (54). Still, both studies exhibited certain limitations. Specifically, individual dose monitoring data were absent for previous years, and the cumulative radiation dose of the radiographers, as assessed using the job-exposure matrix (JEM) may have introduced measurement bias. Additionally, the radiation dose estimates were uncertain (54, 74). To further elucidate the health effects of occupational radiation exposure, two cohort studies were conducted over a five-year period, Liu et al. (54) performed a cohort involving 1265 medical workers exposed to low-dose ionizing radiation over the same duration. Their findings identified a cumulative exposure-response relationship, with an initial increase in platelet count followed by a subsequent decline (54). Additionally, a dose–response relationship was observed, whereby changes in platelet count were directly correlated with the cumulative dose of radiation received. Conversely, Wang et al. (73) found no significant differences in blood cell counts among 375 medical radiation workers engaged in different types of work. No statistical correlation has been found between the long-term cumulative exposure dose and the platelet count for a five-year period (73). The inconsistency in previous research findings may be attributed to short follow-up durations, limited cohort sizes, and a lack of focus on exposure-lag responses. These cohort studies primarily focus on the long-term cumulative exposure-response relationships, while overlooking the exposure-lag-response, which represents the complex interplay between health outcomes and the timing, duration, and intensity of exposure. This concept acknowledges that health effects from exposure may be delayed, with the risk of outcomes depending on both the intensity and timing of previous exposures.

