To address these limitations, we have reviewed the characteristics of prior cohorts and are planning to establish a long-term, enough sample size, prospective cohort study in Chongqing to investigate the exposure-lag response associations and long-term cumulative exposure-response relationships between chronic low-dose ionizing radiation exposure and various adverse health outcomes. Notably, the average annual effective dose of radiation workers monitored in Chongqing from 2016 to 2020 remained below the national individual dose limit and demonstrated an overall downward trend (25, 26, 56).

This study has certain limitations. Data on the physical activity of radiation workers were not collected, which is a recognized risk factor for ocular trauma. Additionally, information on individual ultraviolet (UV) exposure, another significant factor when assessing cataract risk, was not included.

In summary, this study aims to evaluate the health effects of low-dose ionizing radiation exposure among radiation workers in Chongqing. Our study will provide more information on health outcomes and enhance the understanding of work practices and the exposure-lag response association between occupational radiation exposure and the health of radiation workers. It is recommended to further expand the sample size, extend the follow-up time, adopt more advanced statistical methods and improve the dosimetry method in the future, providing a reference for subsequent studies.

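### Filling missing doses with the occupation-year mean can shift effect to wrong lags and overstate the summed effect; the size depends on a missing rate and a within-worker correlation that the article does not give

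*Protocol article*

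**What the plan says.** Section 2.5 (Statistical analysis) of the protocol article names one way to fill a gap in the dose record: "we can use the notional dose to supplement the missing data, which represented the average dose for the same occupation during that year". The completed dose history goes into a DLNM cross-basis, which "will be employed to construct a two-dimensional matrix that integrates radiation dose and lag time, thereby enabling a detailed analysis of the lag structure". The only planned check on missing data is that "analyses will be rerun after excluding cases with missing data".

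The Discussion gives the aim as "to investigate the exposure-lag response associations and long-term cumulative exposure-response relationships", so both the shape over lags and the summed effect are target results.

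The worker's own record is at hand. Section 2.1 says that "their personal dose monitoring data from the Chongqing CDC personal dose monitoring system will be integrated with health data" by personal identification number. Section 2.4 says "The annual effective dosage is defined as the cumulative dose equivalent over four successive monitoring periods (3 months each"), so a single missing reading usually has the same worker's neighbouring readings beside it.

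**The concern.** The fill ignores what is known about the individual. Where some workers in an occupation have persistently higher doses than others, the difference between the true dose and the occupation-year mean is predictable from that worker's other years. Those other years are the other lags in the same regression. They therefore pick up effect that belongs to the filled lag, and lags with no true effect appear to have one. Because the filled doses vary less than the true ones, the summed coefficient also comes out too large. Neither consequence requires missingness to depend on dose.

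At stake are the lag curve, which is the study's distinguishing result, and the cumulative exposure-response that the Discussion puts beside it.

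**Working it through.** **Inputs.** The fill rule, the cross-basis, the linked individual record and the 3-month readings come from sections 2.1, 2.4 and 2.5. The article gives no figure for missing doses, so there is no stated result to reproduce. The following are assumptions:

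- annual doses and six lags (0 to 5);
- a linear effect that sums to 1;
- raw-scale correlation ρ between any two years of the same worker, within occupation and year;
- a share m of worker-years missing, independently across years and unrelated to dose.

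**Step 1: set-up.** Measure dose as a deviation from the occupation-year mean, with variance 1, so a filled dose equals 0. Write q = 1 − m. For the filled dose Z and true dose X at lags k ≠ j:

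- Var(Z_k) = q and Cov(Z_k, Z_j) = q²ρ
- Cov(Z_k, X_k) = q and Cov(Z_k, X_j) = qρ

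The large-sample coefficients are b* = Cov(Z)⁻¹ Cov(Z, X) b. For six lags this gives:

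- summed effect = (1 + 5ρ) / (1 + 5qρ)
- effect at lag k = b_k (1 − ρ)/(1 − qρ) + mρ / [(1 − qρ)(1 + 5qρ)]

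**Step 2: one case in full.** Take ρ = 0.5 and m = 0.20, so q = 0.80.

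- Sum: 3.5/3.0 = 1.167.
- Multiplier on the true lag effect: 0.5/0.6 = 0.833.
- Amount added to every lag: 0.10/(0.6 × 3.0) = 0.056.
- An effect confined to one lag is estimated as 0.833 + 0.056 = 0.889.

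**Step 3: the range.** The last column uses a smooth curve with effects 0.1, 0.2, 0.4, 0.2, 0.1, 0 at lags 0 to 5.

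| ρ | m | Summed effect (true 1) | Gain at a lag with no effect | Single-lag effect kept | Smooth peak kept |
|---|---|---|---|---|---|
| 0.3 | 5% | 1.031 | 0.009 | 99% | 100% |
| 0.3 | 10% | 1.064 | 0.017 | 98% | 100% |
| 0.3 | 20% | 1.136 | 0.036 | 96% | 101% |
| 0.5 | 5% | 1.037 | 0.014 | 97% | 99% |
| 0.5 | 10% | 1.077 | 0.028 | 94% | 98% |
| 0.5 | 20% | 1.167 | 0.056 | 89% | 97% |
| 0.8 | 5% | 1.042 | 0.035 | 87% | 92% |
| 0.8 | 10% | 1.087 | 0.062 | 78% | 87% |
| 0.8 | 20% | 1.190 | 0.106 | 66% | 82% |

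At ρ = 0 the sum is 1, the multiplier is 1 and the added amount is 0, so there is no bias.

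**Step 4: does the worker's own record help?** A separate simulation used ten annual lags, skewed doses, three occupations and an effect peaking at lag 3. The true cumulative effect was 1.00, with 0.03 of it outside lags 1-5. Results at ρ = 0.8 and 20% missing at random:

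| Fill | Peak kept | Effect outside lags 1-5 | Cumulative |
|---|---|---|---|
| Occupation-year mean | 0.81 | 0.32 | 1.21 |
| Own record shrunk toward the occupation mean | 0.99 | 0.04 | 1.00 |

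A plain own mean also did well there (cumulative 0.99), but at ρ = 0 with 20% missing it gave 0.79. When high-dose workers miss more (ρ = 0.8, 20% missing), the cumulative effect was 1.51 with the occupation mean and 1.09 with the shrunk own record.

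**Step 5: the complete-case rerun.** If a visit counts as complete only when all six annual lags are observed, and gaps are independent, the share kept is (1 − m)⁶: 0.95⁶ = 74%, 0.90⁶ = 53%, 0.80⁶ = 26%.

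**The case against.** Several points on the other side stand.

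- **Size is unknown.** A reader might infer that the rule certainly distorts the main result. The documents do not support that: every figure above rests on an assumed missing rate and correlation. Section 2.2 admits only workers who wear their dosimeters consistently, which points to the low-missing rows. If only one 3-month reading in a year is filled, the error in that annual dose is smaller than in the table, which treats the whole year as missing.
- **The lag shape matters.** The single-lag column is the unfavourable case. A natural-spline basis presumes a smooth curve, whose peak keeps at least 97% for correlations up to 0.5. The inflated sum and the gains at lags with no effect are the same for either shape.
- **A check is planned.** With few gaps the complete-case rerun is usable. In the simulation with more missing among high-dose workers (ρ = 0.8, 20% missing) its cumulative estimate was 0.996, so its weakness there is lost precision rather than bias. It nevertheless leaves the main estimate unchanged. The 74/53/26% also rest on independent gaps; clustered gaps would lose fewer visits.
- **The wording is permissive.** That is so, but it is the only fill the article names.

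A second tempting inference is that the plan contradicts itself, because the Discussion says of earlier work that "the cumulative radiation dose of the radiographers, as assessed using the job-exposure matrix (JEM) may have introduced measurement bias", while the notional dose cites one of the same studies. The parallel is only partial. That criticism concerns cohorts without individual monitoring data for earlier years; here a group mean fills gaps in an individually monitored record.

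**Conclusion.** The concern holds as a conditional one. Where doses are correlated within worker, the stated rule moves effect to wrong lags and overstates the summed effect, and missing at random does not protect against this. For a linear effect over six annual lags and correlations of 0.3 to 0.8, the overstatement of the sum is about 3-4% at 5% missing, 6-9% at 10% and 14-19% at 20%. At 20% missing, each lag with no true effect gains about 4-11% of the total. An effect confined to one lag keeps 99-87% at 5% missing and 96-66% at 20%; the peak of a smooth curve is much less affected at low to moderate correlation.

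With few gaps the bias in the sum is small, and with zero correlation and a linear effect it is nil. The calculation does not size the further effect of averaging under the non-linear dose-response that the plan expects ("Given the non-linear relationship between radiation dose and health outcomes, GAM will be applied to assess potential dose–response relationships"). The change is still worth making, because better information is already linked to each worker and both the lag curve and the cumulative effect are target results.

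**What to change.** In the main analysis, replace the notional dose by multiple imputation of the missing monitoring-period dose on the log scale. The model should combine the worker's own other periods with occupation, calendar year and the outcome. Rebuild the cross-basis in each imputed data set and pool with Rubin's rules. A plain own mean should not be used as the substitute. Workers with little or no own record will then draw mainly on occupation and year.

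Report the share of missing doses. Keep the notional dose and the complete-case rerun as sensitivity analyses.

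The cost is analysis-plan wording and some extra programming, with no new data. Two limits remain. Some bias persists if missingness depends on the dose itself (cumulative 1.09 rather than 1.51 in the simulated case). The simulation also tested shrinkage of the own record toward the group mean, not the full multiple-imputation procedure.
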